### 2.10. Fidelity

To ensure the fidelity of the intervention, the project team will ascertain whether the interventions will be delivered as designed. To ensure compliance, the Project team will monitor the duration of usage data on a weekly basis (Friday). If any subject’s weekly usage is <2.5 h, research associates will send a WhatsApp text message as a gentle reminder and investigate if the subject has experienced any technical issues in using the device. The PI will work closely with the research associates to optimize compliance throughout the study period.

### 2.11. Data Management

Participants’ data in both groups will be stored in two separate datasets with an identifier linking these data. Both sets of data will be encrypted using TrueCrypt (http://www.truecrypt.org) (accessed on 1 April 2022). The data from baseline, and the 4-week and 12-week follow-ups will be linked according to personal data. All precautions in data protection will be taken, as suggested by TrueCrypt. To prevent the leakage of personal data, only the PI will have access to the personal dataset. Written consent will be obtained from all participants. An information sheet containing the purpose of this trial and the VeNS procedures, as well as the Modius Stress leaflet, will be provided to all participants. Participants will be informed of their anonymity; withdrawal or non-compliance will not result in any consequences.

### 2.12. Outcome Evaluation (Primary and Secondary Outcomes)

The primary objective of this study is to evaluate the effects of VeNS on participants’ anxiety symptoms in Hong Kong. Secondary objectives include examining the effects between VeNS data usage on insomnia severity and quality of life. All the primary and secondary outcomes will be assessed at baseline and during the 4-week post-treatment and 3-month post-treatment periods for evaluation of immediate and short-term effects [27].

#### 2.12.1. Primary Outcome

##### Anxiety

Anxiety will be assessed using the General Anxiety Scale 7 (GAD-7) [31]. GAD-7 is a widely used, reliable self-reported measurement of generalized anxiety disorder. GAD-7 consists of 7 core items assessing nervousness; inability to stop worrying; excessive worry; restlessness; difficulty in relaxing; easy irritation and fear of awful things happening. Subjects are asked how often they have been bothered by each of the 7 core symptoms of generalized anxiety disorder in the last two weeks on a 4-point Likert scale from 0–3, with 0 = “not at all”, 1 = “several days”, 2 = “more than half the days”, and 3 = “nearly every day”. The total score is obtained by adding up the scores of all the 7 items. Score ranges from 0 to 21, with scores of ≥5, ≥10, and ≥15 representing mild, moderate, and severe anxiety symptom levels, respectively [28]. The GAD-7 has good reliability and validity in the Chinese population [32].

#### 2.12.2. Secondary Outcomes

##### Insomnia Severity

Insomnia will be assessed using the Chinese version of the Insomnia Severity Index (ISI) which consists of 7 items measuring the day and night symptoms of insomnia in individuals. This ISI consists of seven items (1: perceived difficulty; 2: falling asleep; 3: time of awakening; 4: satisfaction with current sleep pattern; 5: interference with daily functioning; 6: noticeability of others’ impact on lack of sleep; 7: degree of perceived distress/concern caused by the sleep problem). Subjects will rate each question on a 4-point Likert scale (0–3); score ranges from 0–28, with 15–21 indicating moderately severe insomnia. ISI has been used in the Chinese population with good psychometric properties, with Cronbach’s alpha 0·81 and item-to-total correlations in the range of 0.34–0.67 [33].

##### Quality of Life

Quality of life will be assessed using the Chinese version of the 36-item Short Form Health Survey (SF-36) [34]. SF-36 include 36 questions related to an individual’s QoL in eight scales: physical functioning (PF), role-physical (RP), bodily pain (BP), general health perceptions (GH), vitality (VT), social functioning (SF), role-emotional (RE), and mental health (MH). The raw scores for each scale are transformed to a scale ranging from 0–100, with higher scores indicating ‘better’ QoL. SF-36 is summarized in two component summary scores, the Physical Component Summary (PCS) and the Mental Component Summary (MCS). This Chinese version of SF-36 is a valid and reliable instrument, with the overall Cronbach’s α coefficient being 0.943, while the Cronbach’s α coefficients for each of the dimensions were all >0.70 [35].

## 3. Statistical Analyses

All statistical analyses will be performed using the statistical software R for Windows (R version 4.1.0). Means and standard deviations (SD) for the continuous variables will be presented, while numbers and percentages for the categorical variables will be shown. A *p*-value < 0.05 is considered statistically significant. Sociodemographic differences between the VeNS group and the sham VeNS group will be analyzed using the chi-square test and t-test. If there are significant differences between sociodemographic factors, covariates will be considered as confounding variables in the analyses. Normality of the primary outcome (GAD-7) scores will be tested using the Shapiro–Wilk test for each combination of factor levels (group and time). A t-test will be used to test the baseline difference. Analysis of variance (ANOVA) with repeated measures will be used to test the group (between-subject factor), time (within-subject factor), and group x time interaction effects of the GAD-7 score between the VeNS group and the sham VeNS group. Post hoc comparisons between groups and time points will be conducted using a *t*-test with the Bonferroni correction. Normality of the secondary outcome scores will be tested using the Shapiro–Wilk test for each time point. For normally distributed outcomes, ANOVA with repeated measures will be used to determine whether the outcome scores are significantly different between pre-and post-test periods. For outcome scores that are normally distributed, a non-parametric Friedman test will be used to test the mean difference. A Cohen’s d effect size for each outcome will be calculated, where d = 0.2, 0.5, and 0.8, corresponding to small, medium, and large effect sizes, respectively. Participants’ total usage time will also be used to investigate the effectiveness of the VeNS on anxiety and total usage time will be used as a continuous covariate in a linear regression model for GAD-7 total score. Missing data will be managed with multiple imputation [36] by adopting the last observation carried forward (LOCF) method.

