### 2.2. Subjects and Sample Size Estimation

Since the collaborative UK study is ongoing, we thus have to take reference of a similar CES study on GAD [23] on ‘Clinical effectiveness and cost minimization model of Alpha-Stim cranial electrotherapy stimulation in treatment seeking pts with moderate to severe GAD’. Participants in the CES group had a significant reduction in GAD-7 score (from baseline 15.77 (3.21) to 10.14 (4.86) (Cohen’s *d* = 1.3)) after 4 weeks of CES treatment.

Considering this trial is a sham-controlled trial, we hypothesize a large effect in the MS group. We used G*power version 3.1.9.7 (https://stats.oarc.ucla.edu/other/gpower/) (accessed on 1 April 2022) nto calculate the target sample size. With a statistical power of 99% and a statistical significance level at 0.05 to detect a large between-groups effect size of 1.3, each group will require 33 subjects. With an estimated attrition rate of 30% during the 12-week post-treatment follow-up, a total sample of 66 is required in this trial.

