### 2.7. Randomization, Allocation, Blinding and Masking

All consenting participants will be listed in alphabetical order according to their surnames and each participant will be assigned a unique identifier. An independent statistician will use a computer-generated list of random numbers (www.random.org) (accessed on 1 April 2022) to ensure concealment of randomization. Randomization will be conducted by an independent statistician off-site using a stochastic minimization program to balance gender, age, and GAD-7 scores of the participants. Block randomization with blocks of 10 (total: 7 blocks) will be used to allocate treatment groups. Participants from each block will be randomly assigned to the active VeNS groups or the sham VeNS groups in a 1:1 ratio. To avoid information flow, participants and research associates will be blinded to the group allocation to minimize potential contamination of the effects of VeNS or subject bias. The Principal Investigator will not be involved in data collection or pre- and post-VeNS measurements. Outcome measurements will be conducted by the research associates. Participants will be asked to guess the grouping (active VeNS vs. sham VeNS) when filling in the face-to-face post-test survey after finishing the 4-week interventions to determine the success of subject blinding [29].

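### Covariates for the GAD-7 analysis are chosen by baseline significance tests, and the stated minimisation factors are not prespecified as covariates

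*Protocol article*

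**What the plan says.** Section 3 (Statistical Analyses) sets significance at p < 0.05, compares the arms on sociodemographic variables by chi-square and t-test, and gives this rule: "If there are significant differences between sociodemographic factors, covariates will be considered as confounding variables in the analyses". For baseline it adds: "A t-test will be used to test the baseline difference". No consequence for the model is attached to that test.

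The primary model in the same section is a repeated-measures ANOVA of GAD-7 with group, time and their interaction. It names no covariate. Baseline is a measurement time (T1, Section 2.1), so on the natural reading baseline GAD-7 is the first level of the repeated outcome.

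Section 2.7 says randomisation is done "using a stochastic minimization program to balance gender, age, and GAD-7 scores of the participants". The same paragraph also specifies blocks of 10, with participants "randomly assigned to the active VeNS groups or the sham VeNS groups in a 1:1 ratio".

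**The concern.** After randomisation a baseline difference with p < 0.05 is a chance event, and the p-value does not show whether the variable predicts GAD-7. A rule keyed to it can bring in a variable with no bearing on anxiety and leave out one that matters. The rule says only that covariates will be considered, so a triggered adjustment is itself left open. Which model produces the primary p-value is therefore not fixed before the data are seen.

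The rule also works against the stated allocation method. Gender, age and GAD-7 were thought important enough to balance. Balancing makes them the variables least likely to differ significantly, so they are the least likely to be adjusted for. At stake are a prespecified primary model, a test that runs at its nominal level, and some precision in a trial of 66 people.

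**Working it through.** **1. The plan's own sample size.** Section 2.2 gives: "With a statistical power of 99% and a statistical significance level at 0.05 to detect a large between-groups effect size of 1.3". A two-sided two-sample t-test at alpha 0.05 with d = 1.3 has 98.8% power with 22 per group and 99.1% with 23, so 23 are needed. Allowing for 30% attrition, 23/0.70 = 32.9, so 33 per group and 66 in total. The plan's figure reproduces, and about 23 completers per arm is the relevant number at the end of follow-up.

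**2. How often chance triggers the rule.** Section 2.6 lists seven clearly sociodemographic items: age, gender, education, marital status, household income, living circumstances and employment. For k independent tests the probability of at least one p < 0.05 is 1 − 0.95^k.
- k = 7: 1 − 0.95^7 = 30.2%.
- k = 5, without age and gender because minimisation suppresses them: 1 − 0.95^5 = 22.6%.

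Independence is an assumption. Education, income and employment are likely to be related, which would tend to lower both figures.

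**3. What happens to minimised factors.** Minimisation was simulated with 46 participants, a biased coin of 0.8, and gender, age and GAD-7 as two-level factors. The baseline-to-post correlation r was 0.3, 0.5 or 0.7, and modest age and gender effects on the outcome were assumed. There were 6,000 trials per setting under no treatment effect.
- A baseline t-test gave p < 0.05 in about 0.5% of trials, both for age and for baseline GAD-7.
- Type I error of the baseline-to-post contrast without covariates was 2.5%, 3.0% and 3.1%.
- Adding age only when it triggered gave 2.5%, 2.9% and 3.0%, so the rule does not repair this.
- With baseline, age and gender in the model it was 4.7%, 4.9% and 5.0%.

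**4. Power with 23 completers per arm, one post-baseline visit.** The effect is in units of the post-treatment SD, the noncentrality is d·√(n/2)/√v, and v is:
- baseline-to-post contrast, equal SDs: 2(1 − r);
- the same contrast with the reference study's SDs in Section 2.2 (3.21 at baseline, 4.86 at 4 weeks): (3.21² + 4.86² − 2r·3.21·4.86)/4.86²;
- ANCOVA on baseline: 1 − r².

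For example, at r = 0.2 the second is (10.30 + 23.62 − 6.24)/23.62 = 1.17 and the third is 0.96.

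| d | r | Contrast, equal SDs | Contrast, reference SDs | ANCOVA |
|---|---|---|---|---|
| 1.3 | 0.2 | 92.6% | 97.8% | 99.3% |
| 1.3 | 0.3 | 95.4% | 98.8% | 99.5% |
| 1.3 | 0.5 | 99.1% | 99.8% | 99.9% |
| 0.8 (assumed) | 0.3 | 61.1% | 74.0% | 79.4% |
| 0.8 (assumed) | 0.5 | 75.6% | 85.4% | 86.5% |
| 0.8 (assumed) | 0.7 | 92.9% | 96.0% | 96.0% |

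The protocol does not give r, so a range is shown. At d = 1.3 and r = 0.7 all three are about 100%.

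**5. Power of the ANOVA with four visits.** This simulation assumes 33 per arm, compound symmetry, the same effect d = 0.5 (assumed) at T2, T3 and T4, and 4,000 trials per setting.

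| Test | Correlation 0.4 | Correlation 0.6 |
|---|---|---|
| ANOVA, group effect | 52.6% | 43.4% |
| ANOVA, group × time | 44.4% | 62.9% |
| T2 contrast adjusted for baseline | 57.4% | 69.6% |

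Against the better planned test the gain is 57.4 − 52.6 = 4.8 points, or 69.6 − 62.9 = 6.7 points. Which planned test is better depends on the correlation.

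**The case against.** Repeated-measures ANOVA with a group × time test is a valid analysis of a randomised trial, and preferring ANCOVA or a mixed model is partly a matter of efficiency. That stands, and the choice of ANOVA is not itself an error.

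A reader might infer that baseline GAD-7 is left out of the primary model. It is not: it is the T1 level, and the interaction uses it. What is missing is its use as a covariate.

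A reader might also infer a serious loss of power. The plan's own effect size does not support that, because at d = 1.3 power stays at about 93% or more in every case tried. Nor should a much larger gain be claimed by comparing the ANOVA with a baseline-adjusted mean of T2 to T4 (85% or 90% in the d = 0.5 setting). Most of that gain comes from averaging three visits with a constant effect, which is a different estimand.

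A third inference would be that ignoring the minimisation factors produces false positives. The simulation shows the reverse.

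Finally, Section 2.7 names both minimisation and blocks of 10. If blocks alone are used, the argument about minimised factors lapses. The objection to the significance trigger does not depend on that. The documents also differ on whether a T3 visit exists (the abstract lists it, Section 2.1 does not), so the four-visit layout in step 5 is an assumption.

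**Conclusion.** The point holds in a limited form. The covariate rule is stated explicitly, so this is not a detail left to an unseen analysis plan, and it makes the primary model depend on chance imbalance: about 23% to 30% of trials would have at least one spurious trigger if the tests are independent. This holds at any effect size.

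If minimisation is the method used, its factors would almost never trigger adjustment. The unadjusted test would then run at about 2.5% to 3% instead of 5%, under the assumed covariate effects.

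The cost in power is secondary. It is slight at the planned d = 1.3 and about 5 to 7 points for the T2 contrast at an assumed d = 0.5. A smaller effect is plausible, because Section 2.2 reports 1.3 beside a before-and-after change within one treated group and then uses it as a difference between arms. The correlations, the smaller effects and the simulated covariate effects are assumptions, not figures from the protocol.

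**What to change.** In Section 3, delete the sentence that ties covariates to significant baseline differences, drop the baseline chi-square and t-tests, and present baseline data descriptively. Replace them with a prespecified model, for example: the GAD-7 model has the post-baseline visits as outcome and includes arm, visit, arm × visit, baseline GAD-7, age and gender; no covariate is added because of a baseline test. Use the same covariates for ISI and SF-36, each with its own baseline. Section 2.7 should also say whether minimisation or blocks of 10 is used, so that the model can be matched to the allocation.

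The cost is a few lines of wording and about three degrees of freedom. All the variables are already collected.

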### 2.4. Eligibility Criteria

To obtain a homogenous sample, the inclusion criteria will be: (1) having a GAD-7 score > 10; (2) ethic Chinese, aged 18–60 years; (3) able to understand/read Chinese; (4) having an Insomnia Severity Index < 14; (5) able to provide written informed consent; (6) having Wi-Fi and Bluetooth network in iOS/Android mobile phones; (7) able to attend the face-to-face demonstration session for proper use of the MS device and return-demonstrate to research assistants in the training venue (Integrative Health Clinic, School of Nursing, The Hong Kong Polytechnic University; (8) willing to engage with the project team on a weekly basis via zoom meetings/WhatsApp/telephone to ensure compliance, proper usage of the MS device and report any technical issues; (9) not undergoing any extreme lifestyle changes that may impact on sleep quality (e.g., dietary changes/increase/decrease exercise levels) throughout the study period; (10) not taking any prescribed/over the counter anxiolytics.

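### For ISI and SF-36, Shapiro–Wilk pretests of raw scores, including an ISI baseline cut by eligibility, choose the test, and neither branch names an active-versus-sham comparison

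*Protocol article*

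**What the plan says.** All references are to the protocol article.

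- **Pretest, secondary outcomes (section 3):** "Normality of the secondary outcome scores will be tested using the Shapiro–Wilk test for each time point". Two methods follow. Repeated-measures ANOVA is for normally distributed outcomes and is described as testing whether scores differ before and after treatment. The other method is a Friedman test. As printed, both sentences carry the same condition; the sensible reading is that the word *not* is missing from the second.
- **Pretest, primary outcome (section 3):** "Normality of the primary outcome (GAD-7) scores will be tested using the Shapiro–Wilk test for each combination of factor levels (group and time"). No action is tied to the result. The repeated-measures ANOVA is then stated without condition, and it covers "group x time interaction effects of the GAD-7 score between the VeNS group and the sham VeNS group".
- **Eligibility (section 2.4):** "having an Insomnia Severity Index < 14" and "having a GAD-7 score > 10".
- **Scales (section 2.12):** for ISI, "score ranges from 0–28, with 15–21 indicating moderately severe insomnia". For SF-36, "The raw scores for each scale are transformed to a scale ranging from 0–100", with no entry cut-off on any scale.
- **Secondary hypotheses (section 1.2.2):** improvement in insomnia and quality of life under active VeNS with higher usage, and no change under sham.

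**The concern.** The written rule lets the trial data choose the analysis of each secondary outcome, and it has four weaknesses.

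1. It tests the wrong quantity. ANOVA needs approximately normal residuals, not normal raw scores at each visit. A score taken before treatment says nothing about whether the active-versus-sham comparison is valid.
2. For ISI, eligibility shapes one of the tested distributions. Baseline ISI can only be an integer from 0 to 13, so the pretest may reject because of who was admitted.
3. The pretest is repeated at every time point, which adds chance rejections. The rule does not say what happens when time points disagree.
4. The fallback cannot answer the trial's question. A Friedman test compares time points and has no term for treatment group.

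At stake is the randomised comparison for ISI and SF-36. An outcome could be moved to a test that cannot separate active from sham, and different outcomes could be analysed by different methods picked after the data are seen.

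**Working it through.** **Numbers tested.** Section 2.2 plans 33 per group, 66 in total. This reproduces: a two-sided t-test with d = 1.3, alpha 0.05 and power 99% needs 22.75, so 23 per arm; 23 / 0.70 = 32.9, so 33 per arm and 66 in total. The secondary pretest is stated per time point, not per group and time point, so pooled n = 66 is the natural reading at baseline. n = 33 is shown in case it is run by arm.

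**False alarms with normal data.** The abstract lists four time points; sections 2.1 and 2.12 list three. With independent tests at 0.05:

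- three time points: 1 − 0.95³ = 0.14
- four time points: 1 − 0.95⁴ = 0.19

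Repeated scores are correlated, so these figures are approximate. They apply to ISI and to each SF-36 score.

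**Baseline ISI under the entry rule.** The documents give no mean or SD for ISI, so a range is assumed. Scores are integers k with probability proportional to Φ((k + 0.5 − μ)/σ) − Φ((k − 0.5 − μ)/σ), limited to 0–13 with the cut or to the stated 0–28 without it. Shapiro–Wilk is run at 0.05. Rejection rates:

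| Mean (SD) before the cut | n = 66, cut at < 14 | n = 66, no cut | n = 33, cut at < 14 |
|---|---|---|---|
| 7 (3) | 21% | 17% | 9% |
| 8 (4) | 56% | 14% | 18% |
| 10 (4) | 95% | 10% | 48% |
| 12 (5) | 100% | 7% | 74% |
| 14 (5) | 100% | 6% | 91% |
| 16 (5) | 100% | 6% | 98% |

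At mean 6, SD 4 and n = 66, the rates are about 40% with the cut and 38% without it. There the floor at zero drives rejection, not eligibility. The cut clearly dominates from a mean of about 8 upwards.

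**What the Friedman branch would test.** The property can be shown on GAD-7-type scores, the only outcome with a mean and SD in the documents. Two identical arms of 33 were simulated at three time points, with entry limited to 11–21 and a correlation of 0.6 with baseline. The pooled Friedman test rejected in 99% of trials when scores before the cut had mean 8 and SD 5, because selected high scores regress to the mean. It rejected in 5% when they had mean 15.77 and SD 3.21. There was no treatment effect in either case, so a significant result says nothing about active versus sham.

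**Whether truncation itself breaks the parametric comparison.** In the same two settings, a t-test comparing change between arms had a type I error of 4.7% and 5.0%. The pretest can therefore discard a comparison that works.

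**The case against.** A reader might infer that the primary analysis is also chosen by the data, since GAD-7 is cut at entry and also pretested. The documents do not support this. The GAD-7 ANOVA is unconditional, no switch follows from its Shapiro–Wilk test, and truncation alone left the type I error near 5%. That pretest has no stated consequence.

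A reader might also infer that normality must fail at baseline by construction. That depends on the population screened. If ISI centres well below 14, rejection is modest and the cut adds little (21% against 17% at mean 7, SD 3). The truncation argument also reaches ISI only. SF-36 has no cut-off and is exposed just to the repeated testing and the choice of test.

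The strongest objection is that the pretest does not cause the loss of the between-arm test. The ANOVA branch for secondary outcomes names no group term either, so removing Shapiro–Wilk alone would not restore the comparison. This stands, and the remedy has to name the comparison. It is also true that the route to Friedman exists only once the missing *not* is read in. But supplying that word would make the rule workable and leave each of the weaknesses in place.

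One could run Friedman within each arm to match the secondary hypotheses. A significant change in one arm and none in the other is still not a test of the difference between arms.

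**Conclusion.** The point holds for the secondary outcomes. Section 3 ties the analysis of ISI and SF-36 to pretests of raw scores at each time point, and neither resulting branch states an active-versus-sham comparison.

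At baseline with 66 participants, the chance that ISI fails the pretest runs from about 20% to 100%. The range rests wholly on assumed means and SDs, and eligibility is the main cause only when the mean before the cut is about 8 or higher. The 14% to 19% false-alarm rate assumes independent tests. The Friedman consequence assumes that the second branch means scores that are not normal.

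The primary GAD-7 analysis is not affected. The plan should be changed, but the consequence is confined to secondary outcomes.

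**What to change.** In section 3, delete the Shapiro–Wilk step and the Friedman fallback for the secondary outcomes. Name in advance one between-group analysis for ISI and SF-36, used whatever the score distribution: ANCOVA, or a mixed model of post-baseline scores with baseline as covariate. State the active-versus-sham difference at each follow-up as the target. The target should not be a group-by-time interaction on post-baseline scores alone: if the benefit is constant over follow-up, that interaction is zero and its power is only the 5% significance level.

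Check residuals, and pre-state one distribution-free sensitivity analysis of active versus sham, for example a permutation test. The GAD-7 Shapiro–Wilk step can be removed or labelled descriptive, since nothing depends on it.

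The cost is a few sentences and one additional analysis. No extra data or participants are needed.

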## Abstract

The prevalence of symptoms of anxiety is increasing, especially during the COVID-19 pandemic. A home use transdermal neurostimulation device might help to minimize the severity of anxiety disorder. To the best of our knowledge, there is no clinical trial using transdermal neurostimulation to treat individuals with symptoms of anxiety in Asia. This gives us the impetus to execute the first study which aims at evaluating the efficacy of Electrical Vestibular Stimulation (VeNS) on anxiety in Hong Kong. This study proposes a two-armed, double-blinded, randomized, sham-controlled trial including the active VeNS and sham VeNS group. Both groups will be measured at baseline (T1), immediately after the intervention (T2), and at the 1-month (T3) and 3-month follow-up (T4). A total of 66 community-dwelling adults aged 18 to 60 with anxiety symptoms will be recruited in this study. All subjects will be computer randomised into either the active VeNS group or the sham VeNS group in a 1:1 ratio. All subjects in each group will receive twenty 30 min VeNS sessions during weekdays, which will be completed in a 4-week period. Baseline measurements and post-VeNS evaluation of the psychological outcomes (i.e., anxiety, insomnia, and quality of life) will also be conducted on all participants. The 1-month and 3-month follow-up period will be used to assess the long-term sustainability of the VeNS intervention. For statistical analysis, ANOVA with repeated measures will be used to analyze data. Missing data were managed with multiple mutations. The level of significance will be set to *p* < 0.05. Results of this study will be used to determine whether this VeNS device can be considered as a self-help technological device to reduce perceived anxiety in the general population in the community setting. This clinical Trial was registered with the Clinical Trial government, identifier: NCT04999709.

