#### 1.2.2. Secondary Hypotheses

Participants who have higher data usage in the active VeNS group will have statistically significant changes in insomnia severity and improved quality of life after the 4-week treatment that will be maintained during the 12-week follow-up. There will be no change in insomnia and quality of life in the sham VeNS group immediately after treatment and at the post-treatment follow-up at 12-weeks.

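### The secondary insomnia and quality-of-life claims rest on up to eleven scores, each at p < 0.05, with no SF-36 score named as decisive and no error control across outcomes (minor)

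*Protocol article*

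**What the plan says.** Section 1.2.2 words the secondary hypothesis as a claim of significance: "Participants who have higher data usage in the active VeNS group will have statistically significant changes in insomnia severity and improved quality of life", with the effect holding through the 12-week follow-up. It does not call this exploratory.

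Section 2.12.2 defines the measures. Insomnia has one score, the ISI total. For quality of life, "SF-36 include 36 questions related to an individual’s QoL in eight scales", and there are also two summary scores, PCS and MCS. That makes up to ten SF-36 scores. The section does not say which of them decides whether quality of life has improved.

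Section 3 sets a single threshold, "A *p*-value < 0.05 is considered statistically significant", and the Abstract repeats it. For the secondary scores, "ANOVA with repeated measures will be used to determine whether the outcome scores are significantly different between pre-and post-test periods". The only multiplicity correction in the article is Bonferroni. It appears directly after the GAD-7 ANOVA, covers post hoc comparisons of groups and time points, and is not extended across outcomes.

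**The concern.** The article joins a claim of significance to a threshold applied score by score. For insomnia this is harmless, because there is one score. For quality of life the claim has no fixed criterion: the article neither says which SF-36 scores will be tested nor which would settle the matter. A later report could call quality of life improved on the strength of whichever score fell below 0.05, and nothing in the article would rule that out.

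What is at stake is how far a secondary finding can be trusted. The primary GAD-7 analysis is not affected.

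**Working it through.** The plan states no error rate across the secondary outcomes, so there is no figure to reproduce. The check asks what the stated threshold implies.

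**Inputs from the article.** Alpha 0.05 per test (section 3 and Abstract; sidedness not stated, taken as two-sided). ISI: 1 score. SF-36: 8 scales + 2 summaries = 10. Total 1 + 10 = 11.

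**Assumptions not in the article.** A common correlation r between the test statistics, run from 0 to 0.8. One test per score. Each test is a valid 5% test of the treatment effect. No true effect on any score counted.

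**Method.** For independent tests the chance of at least one false positive among k is 1 − 0.95^k:

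- k = 11: 1 − 0.95^11 = 0.431
- k = 10: 1 − 0.95^10 = 0.401
- k = 3: 1 − 0.95^3 = 0.143
- k = 2: 1 − 0.95^2 = 0.0975

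For correlated tests, 400,000 draws of k equicorrelated normal statistics were simulated, counting any |z| > 1.96.

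| Scores tested | r = 0 | r = 0.5 | r = 0.8 |
|---|---|---|---|
| ISI + ten SF-36 (11) | 0.43 | 0.30 | 0.18 |
| Ten SF-36 only (10) | 0.40 | 0.29 | 0.17 |
| ISI + PCS + MCS (3) | 0.14 | 0.125 | 0.10 |
| PCS + MCS only (2) | 0.10 | 0.09 | 0.08 |

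**Direction.** Counting only false positives that favour active treatment, eleven scores give 0.24, 0.15 and 0.09 at r = 0, 0.5 and 0.8. ISI, PCS and MCS give 0.07, 0.06 and 0.05. The matching nominal rate for one test is 0.025.

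**Both required.** If the claim needs ISI and at least one of the ten SF-36 scores to be significant, and neither domain is affected, the rate cannot exceed the 5% of the ISI test alone. With independence it is 0.05 × 0.401 = 0.020. By simulation it is about 2–4% for r from 0 to 0.8.

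**One domain truly affected.** If insomnia really improves and quality of life does not, the ISI condition gives little protection. The risk then moves towards the SF-36 rows of the table: 17–40% over ten scores, 8–10% over PCS and MCS.

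**The case against.** The strongest reply is that this is an omission from a condensed article with a single primary outcome, and that a key score or testing order is commonly left to the SAP. That would hold if the article were silent. It is not: it fixes the threshold, says where Bonferroni applies, and predicts significance for the secondaries. The combination is a rule the article does state. The reply does lower the severity, since the primary error rate is unaffected.

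Four stronger readings are tempting, and the article does not support them.

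- *A false secondary claim has about a 30% chance.* This needs all eleven scores tested, a correlation near 0.5, errors counted in both directions, and any single hit counted as success. The article gives no correlations and does not say which SF-36 scores will be tested.
- *The plan's rule is that one significant SF-36 score out of ten suffices.* No such rule is written. The fault is that no rule is given.
- *The insomnia-and-quality-of-life claim as a whole is inflated.* Section 1.2.2 joins the two. If both are required and neither is affected, there is no inflation above 5%. But no decision rule ties them together, and the quality-of-life half stays undefined either way.
- *The verdict on the device as a self-help option is at risk.* The Abstract and section 6 tie that verdict to perceived anxiety, which GAD-7 measures.

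One further objection stands in full. Section 3 describes the secondary test as a pre/post comparison, and section 1.2.2 speaks of higher-usage participants in the active arm. The calculation models neither. A pre/post test can be significant through change over time that has nothing to do with treatment, so the figures above do not give the error rate of the analysis as worded.

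**Conclusion.** The point holds as a minor one. A confirmatory-style secondary claim is paired with an unadjusted 0.05 per score, and its quality-of-life half can be read from up to ten scores with none named.

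The size depends on choices the article leaves open, so it should be quoted as a range with its assumptions: from about twice the nominal level (three scores, highly correlated) to between eight and nine times (eleven independent scores, 0.43/0.05 = 8.6), and no inflation if both domains must succeed and neither is affected. All of this assumes one valid between-group test per score; separate tests at several time points would add to it.

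**What to change.** In section 3, and in the wording of section 1.2.2:

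1. Name one SF-36 score in advance, for example MCS, as the score that decides the quality-of-life claim. With a between-group test, this returns that claim's false-positive rate to about 5%.
2. Control error over the two secondary claims, ISI and the named score. Holm would do: the smaller p-value is compared with 0.05/2 = 0.025 and, if that succeeds, the larger with 0.05. Alternatively, label the secondaries as supportive and drop the language of significance from section 1.2.2.
3. Report the summary score not named, the eight scales and other time points as exploratory estimates with confidence intervals.
4. Base the secondary claims on the group-by-time comparison, because the pre/post wording does not test the treatment effect. Without this step, the first two would give confirmatory status to the wrong comparison.

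Making the secondaries conditional on GAD-7, with ISI tested first, is optional. Its drawback is that section 2.4 admits only people with ISI below 14, so there is limited room to improve and a null ISI result would block the quality-of-life test.

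The cost is a short paragraph and a reworded hypothesis, with no extra data or participants. What is given up is any confirmatory claim on the other SF-36 scores.
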